**Fig. 1 Fig1:**
[figure not shown]
Study flowchart

Timelines are presented in Table 1. After 3 to 6 months of rehabilitation, if patients are not satisfied, they will be allocated to the PRP or saline group. The follow-up will last 1 year after the intervention (intervention is at month 0), with endpoints at − 3/− 6, 0, 3, 6, and 12 months of follow-up.

**Table 1 Tab1:** Participant timeline

		Study period								
	Enrolment	Rehabilitation				Allocation	Post-allocation			Close out
**Timepoint in months**	− 3^¼^ to − 6^¼^	− 3 to − 6	− 1^½^ to − 4^½^	0 to − 3	0*	0	¼	3	6	12

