**Interventions**										
Organize rehabilitation		x								
Rehabilitation checkpoint			x	x	x			x	x	
Needling (with PRP or Saline)							x			

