### Randomization and blinding

The allocation will be performed using computer-generated random number by serials of 4 patients blocks on a 1:1 ratio. Four strata will be used: (i) age 18–39 and absence of lesion on the superficial epicondylar tendon; (ii) age 18–39 and concomitant lesion on the superficial epicondylar tendon; (iii) age 40–65 and absence of lesion on the superficial epicondylar tendon; and (iv) age 40–65 and concomitant lesion on the superficial epicondylar tendon. The sponsor-investigator (AS) will generate 10 computerized allocation sequences. The secretary will randomly select one of those sequences for the study. The sponsor-investigator will enroll the participants and will perform the intervention 3 months after the recruitment. Patients will be allocated to a group at the time of the intervention, and only if the rehabilitation process was not successful. The unblinded co-investigator (MF) will access to the allocation on a sequentially numbered list and prepare the injection for the intervention in an opaque syringe (blinded content for AS). It is worth noting that this co-investigator will not take care of the patients subsequently.

This study is quadruple-blinded. Blinding concerns (i) the participants and (ii) the principal investigator (AS) during the intervention, (iii) the outcome assessment, and (iv) the statistical analysis. A complete masking of the intervention will allow the blinding of the participant and the principal investigator for the intervention and the outcome assessment. First, for all patients, the co-investigator (MF) will perform a blood puncture in room A. He will then go in room B and, depending of the allocation, prepare the PRP or turn-on the centrifuge for 5 min (sham PRP preparation). After that, he will prepare an opaque syringe containing either PRP or saline solution. In room A, the principal investigator will perform the ultrasound-guided fenestration of the ECRB tendon. During the fenestration, he will use the opaque syringe and inject the blinded content into the ECRB tendon. The statistical analysis (iv) will be performed by the principal investigator using a sham allocation list. Once the statistical analysis is completed, the true allocation list will replace the former list.

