### Study treatments and interventions

All patients should perform the rehabilitation protocol during the 3 months following the intervention (Additional file 1). During this protocol, all patients will perform global and specific active strengthening and self-stretching, focused ESWT, focused therapies, Kinesio taping, and orthotics. After 3 months, if a constant but insufficient symptom alleviation is observed, the rehabilitation program could be lengthened by 3 months (i.e., rehabilitation months 4–6). If a radiological ECRB lesion persists on ultrasonography, shockwave therapy will be performed during rehabilitation months 4–6. If the rehabilitation protocol enables symptom disappearance (i.e., the rehabilitation was successful), the intervention will not be performed. If, for any other reason, the intervention cannot be performed, the patient will be dropped out of the study.

It is not clear whether PRP should be used or not as an adjuvant procedure to tendon needling. An injection of saline solution during the procedure as comparator seems the most logical, because it (i) allows a proper blinding of both patient and physician, (ii) has no deleterious effects on tendon repair (contrary to active products such as corticosteroids) and therefore no influence on clinical outcomes, and (iii) has no potential side effects.

In both groups, the intervention will occur under strict aseptic conditions as following: First, a local anesthetic blockade of the radial nerve under the arcade of Frohse will be performed under ultrasonographic control. Then, an ultrasound-guided needling of the ECRB tendon will be performed, using the fenestration technique: 25 repetitions with a 20-gauge needle. During the procedure, the lesion will be fulfilled with either PRP (experimental group) or saline solution (control group). The PRP (ACP Arthrex) will be prepared using a double syringe system under the manufacturer’s recommendation. From 15 ml of peripheral blood, the PRP will be extracted on site using centrifugation (1500 rpm 5 min), as recommended by the manufacturer. After the intervention, the learned self-exercises should be continued as long as necessary. The use of ice and pain medication with paracetamol or opioids (tramadol, codeine) will be used to manage pain, if necessary.

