### Statistical analysis

The difference in primary outcome (pain improvement from baseline to 3 months post-intervention) between the treatment and control groups will be evaluated using the unpaired Student *T* test (or the Wilcoxon rank test when appropriate). The difference in secondary outcomes (changes from baseline to other time points) between the treatment and control groups will be evaluated with the appropriate statistical test (categorical variables: chi-squared, Fisher’s exact; continuous variables: Student’s or Wilcoxon rank tests). All analyses will be performed with an intention-to-treat analysis. Estimates of effect, 95% confidence intervals and descriptive *p* values will be reported whenever possible. In addition, graphs will be presented whenever possible.

Because the intervention is not considered at risk, not interim analysis is planned. However, in order to re-adjust the sample size calculation, it is planned to re-assess the standard deviation of the primary outcome for the 40 first allocated patients.

In case of missing data on the primary outcome, patients will be withdrawn. Patients with missing data for any of the secondary outcomes will be kept on the study, but excluded from the corresponding analysis.

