### Data collection and management

All data collected in this trial will be recorded on standardized paper case report forms (CRF). The sponsor-investigator (AS) is responsible for ensuring that all parts of the CRFs are filled in correctly. The two used questionnaires, SANE score [22] and the PRTEE score [25], are commonly used validated tools. The principal investigator is responsible for ensuring that all parts of CRFs are filled in correctly. Any change or correction to the CRF should be dated and initialed. Each CRF must be signed at least once by the investigator.

The physician closely supervises the participants during rehabilitation visits in order to improve their compliance to the rehabilitation program (CF above). In case of missed appointment, a new date will be proposed by phone. If participants deviate from protocol, the remaining follow-up visits will still be performed and the corresponding data will be collected.

All protocol-required information collected during the trial must be entered by the sponsor-investigator, or designated co-investigator, in the CRF. The CRF pages should be completed and signed the same day that a trial subject is seen for any of the trial procedures. For all CRFs, a copy is immediately stored on the digital secured server of the principal investigator. In order to ensure that the database reproduces the CRFs correctly, the sponsor-investigator, or designated representative, will perform a double entry of the data on two distinct CSV files. For each visit, a different CSV file will be created. Then, the CSV files will be compiled on a database using “R” software (R Foundation for Statistical Computing, Vienna, Austria). The quality of the data entered is guaranteed using “R” software as follows: (i) the duplicate CSV for double entry are digitally compared, and discordant results identified, and (ii) the completeness, validity, and plausibility of the data will be tested for each variable. In case of discordant data, the principal investigator will clarify or correct the problematic data. All eventual changes will be recorded. If no further corrections have to be made in the database, the latter will be closed and used for statistical analyses. All important trial documents (e.g., CRFs) will be archived for at least 10 years after completion of the clinical trial.

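### Withdrawing patients with no month-3 pain score conflicts with the stated intention-to-treat analysis and makes the primary comparison complete-case

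*Protocol article*

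**What the plan says.** The Statistical analysis section sets the analysis population: "All analyses will be performed with an intention-to-treat analysis". Its last paragraph then gives two rules for missing data. For the primary outcome: "In case of missing data on the primary outcome, patients will be withdrawn". For the others: "Patients with missing data for any of the secondary outcomes will be kept on the study, but excluded from the corresponding analysis".

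Three other places bear on who remains in the trial:

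- Study treatments and interventions, in the paragraph on rehabilitation: "If, for any other reason, the intervention cannot be performed, the patient will be dropped out of the study".
- Randomization and blinding: "Patients will be allocated to a group at the time of the intervention, and only if the rehabilitation process was not successful". The Study design text likewise sets the intervention at month 0. Table 1, as extracted, marks randomisation under month 0 but needling under month ¼.
- Data collection and management: "If participants deviate from protocol, the remaining follow-up visits will still be performed and the corresponding data will be collected".

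**The concern.** A randomised patient without a month-3 pain score cannot be both analysed by intention to treat and withdrawn. The contrast with the rule for secondary outcomes suggests that withdrawal means leaving the study, not just one analysis. This is a stated rule that conflicts with the stated population, so it is not a detail left to an analysis plan.

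The primary endpoint is self-reported pain at a single visit, and whether a patient supplies that score may depend on how the elbow is doing. If that dependence differs between arms, comparing only those who supplied a score no longer estimates the effect in the patients who were randomised. Recruiting more patients to allow for dropout restores precision but does not remove such a bias. Withdrawal would also discard month-6 and month-12 pain scores that carry information about the missing month-3 value.

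**Working it through.** **Inputs (Sample size section and Abstract).** Power 95%, significance level 5% (taken as two-sided, which reproduces the plan), difference 10 percentage points (50% against 60% improvement), SD 10 points, dropout 10%, one in four included patients randomised, 1:1 allocation, at least 58 randomised.

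**The plan's own figure.**

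- Per arm: 2 × [10 × (1.960 + 1.645) / 10]² = 25.99, so 26, or 52 in total.
- With 10% dropout: 52 / 0.9 = 57.8, so 58 randomised, 29 per arm.
- Included: 58 / 0.25 = 232, as stated.

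The plan therefore expects 58 − 52 = 6 randomised patients without a usable primary outcome. Power with 26 completers per arm is 95.0% by the normal approximation and 94.2% for the t test. Power is not the problem.

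**Bias.** Let m be the number missing in an arm and g the number of points by which their mean improvement falls short of that arm's completers (P = PRP, S = saline). The complete-case difference minus the all-randomised difference is

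bias = (g_P × m_P − g_S × m_S) / 29.

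A positive value overstates PRP. The documents give neither m by arm nor g, so every row below is an assumption.

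| Missing PRP / saline | Assumption | Bias (points) |
|---|---|---|
| 3 / 3 | same shortfall in both arms | 0 |
| 3 / 3 | all six improve 0% (g = 60 and 50) | (180 − 150) / 29 = 1.0 |
| 3 / 3 | all six improve 25% (g = 35 and 25) | (105 − 75) / 29 = 1.0 |
| 4 / 2 | g = 20 in both arms | 40 / 29 = 1.4 |
| 3 / 3 | g = 20 in PRP only | 60 / 29 = 2.1 |
| 5 / 1 | g = 20 in both arms | 80 / 29 = 2.8 |
| 6 / 0 | g = 20 in PRP | 120 / 29 = 4.1 |

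Swapping the arms in the rows with g = 20 reverses the sign. With no true effect and SD 10, the normal approximation gives a two-sided type I error of about 17% in the 5/1 row and 32% in the 6/0 row.

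**Timing.** If allocation and needling coincide, as the Study design and Randomization and blinding sections have it, a patient who cannot be needled will mostly leave before being randomised. That does not disturb the comparison. If about a week separates them, as the Table 1 columns suggest, the same rule could remove randomised patients.

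**The case against.** The strongest case against is that little may be lost in practice. Patients, the injecting physician and outcome assessment are blinded, which makes strongly arm-dependent loss less likely. The co-investigator who prepares the syringe is unblinded but does not look after the patients afterwards. Missed appointments are to be rebooked. The 10% loss is already in the sample size. The word for withdrawal stands in an analysis section and may mean only removal from the analysis. The choice of missing-data model is commonly left to an analysis plan, which is not shown. These points lower the likely size of any bias, and they leave the loss of later data as a literal reading rather than a certainty. They do not reconcile the two sentences.

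Three stronger readings are tempting but not supported:

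- *The bias is about half the target difference.* Three saline patients with no improvement would lower the saline mean to (26 × 50 + 3 × 0) / 29 = 44.8%, a shift of 5.2 points. That changes one arm only. Giving the three missing PRP patients the same outcome yields 26 × 60 / 29 = 53.8%, so the contrast is 9.0 instead of 10 and the bias about 1.0 point. Zero improvement also lies five of the plan's SDs below the saline mean.
- *Dropping patients who are not needled breaches intention-to-treat.* That rule sits among the rehabilitation rules, and the text allocates at the time of the intervention. Only the Table 1 columns point the other way, and their positions may have been disturbed in extraction.
- *The data collection rule flatly contradicts withdrawal.* It concerns protocol deviations, not missing values as such. It is supporting evidence only.

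**Conclusion.** The conflict over a missing primary outcome stands on the text alone: as written, the primary analysis is complete-case under an intention-to-treat label. About 6 of 58 randomised patients would be affected at the planned dropout. The resulting bias could be nil. It is about 1 point when three patients per arm share the same poor outcome, and about 2 to 4 points in the clearly uneven scenarios with a 20-point shortfall, against a target of 10. These sizes rest on assumed numbers and outcomes of missing patients. The documents fix neither the size nor the direction.

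The rule on patients who cannot be needled is a secondary and conditional matter. It becomes a breach only if patients can be randomised and then not needled, and the document is inconsistent on whether that can happen.

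**What to change.** Replace the sentence on missing primary outcomes with: *Patients with a missing month-3 value remain in follow-up, and all randomised patients are analysed in their allocated group.*

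Estimate the month-3 contrast with a likelihood-based repeated-measures model on the contraction pain score at months 0, 3, 6 and 12. All four are already scheduled. Treating month 0 as one of the outcomes lets patients with no later score contribute as well. Add one sensitivity analysis for data missing not at random, for example multiple imputation with a stated shift applied to the imputed values. The planned t test can stay as a supporting analysis.

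Reconcile Table 1 with the Study design and Randomization and blinding sections on when randomisation and needling take place. State that the rule on patients who cannot be needled does not remove anyone already randomised from follow-up or analysis.

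The cost is protocol wording and slightly more analysis work. The figures of 58 and 232 do not change, and no patients or visits are added.

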## Background

The conservative management of lateral epicondylitis is known to be a difficult-to-treat annoying condition. The first-line conservative management includes physical therapies, orthotics [1], and extracorporeal shock wave therapy (ESWT) [2]. The success rate of ESWT for lateral epicondylitis depends mainly on the protocol that is followed. For instance, poor results have been observed with too low energy [3]. Focused ESWT has been showed to be as effective as surgical tenotomy [4].

Infiltrative therapies might be proposed in case of persistent symptoms. It has been well established that corticosteroids are efficient in the short-term but deleterious in the long-term [5, 6] likely for degenerative purposes [7]. Prolotherapy, autologous blood or botulinic toxin injections, and others infiltrative therapies are less studied and are therefore not clearly supported by the current literature [8–10]. Stem cells might be an appropriate alternative in the future [11].

Platelet-rich-plasma (PRP) is nowadays widely used for tendinopathies, considered as safe, and currently supported by the strongest scientific journals [12]. However, the potential benefits of PRP are discordant, especially concerning the elbow. Even if the superiority of PRP over corticosteroids is well established [13], the efficacy of PRP in addition to tendon needling or fenestration compared to tendon needling or fenestration alone is still controversial [14–19].

Several factors have been advocated to influence PRP outcomes. The most relevant ones are direct mechanical action of the needle and fenestration technique, number of PRP injections, cell counts (platelets, white blood and red blood cells), activation of the platelets, concomitant local anesthetic use, peri-interventional use of NSAIDs and corticosteroids, concomitant rehabilitation, or a contrario immobilization [20]. The positive results observed in the previous reported studies remain debatable as they can be [17, 18] related to either PRP, fenestration [21], or any of the abovementioned confounding factors.

The first aim of this study is to determine the proportion of patients that would need an infiltrative technique after a proper rehabilitation protocol including physical therapies, focused ESWT, and orthotics and Kinesio taping for all patients. Our second aim is to establish whether PRP as adjuvant therapy to fenestration would increase clinical outcomes.

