### Study design

This study will include 232 patients and will be conducted in two steps (Fig. 1). The first step consists in an observational case series. During this step, all patients will benefit from a proper rehabilitation including epicondylar stretching and eccentric strengthening; periscapular and global tonification; postural adjustment; manual therapies including trigger points release, epicondylar taping, or bracing; and focused shockwave therapy (Additional file 1). The second step consists in a case-control superiority trial randomized 1:1 between PRP (intervention group) and saline (control group) injections. A stratification is planned on age and lesion pattern.

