### Outcome measurements and assessments

The primary endpoint is the pain improvement between months 0 and 3 on a 0–10 visual analog scale (VAS) during a maximal strength isometric contraction of the extensor carpialis brevis muscle. Rationale: most specific clinical test in order to reproduce pain triggered by the tendon target of the intervention. Most clinical effects of the PRP use are awaited after 3 months of follow-up [18, 22]. The tendon healing will be evaluated with ultrasound in secondary outcomes. It was decided to use clinical parameters as primary outcome, because some pathological elements might persist on ultrasound after healing. Although the sensitivity of ultrasound is high, it does not reach 100% [23, 24].

Secondary endpoints:

Proportion of patients for which the tendon needling is not necessary after rehabilitation protocol

Clinical scores at − 3, 0, 3, 6, and 12 months of follow-up: (i) pain on a 0–10 (VAS) during a maximal strength isometric contraction at other timepoints; (ii) pain on a 0–10 VAS scale at rest; (iii) Single Assessment Numeric Evaluation (SANE) score; (iv) Patient-Rated Tennis Elbow Evaluation (PRTEE) score; and (v) maximal grip strength on Jamar test.

Ultrasonographic aspects of the epicondylar tendons at − 3, 0, 3, 6, and 12 months of follow-up: (i) volume of the lesion in mm^3^; (ii) Doppler reaction classified at the proportion of the tendon marked with the Doppler signal; (iii) solution of continuity in mm^3^; (iv) tendon thickness in mm; (v) concomitant superficial lesion and volume in mm^3^; and (vi) pain on a 0–10 VAS scale during sonopalpation.

It is worth noting that all post-intervention outcomes will be compared to their baseline values at month 0 in order to evaluate their net improvements.

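### Read literally, the complete-case rule takes patients with unknown rehabilitation status out of the denominator of the rehabilitation success proportion, so the answer to the first aim can be biased, with more room upward than downward

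*Protocol article*

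**What the plan says.** All references are to the protocol article.

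- **Aim.** The Background states: "The first aim of this study is to determine the proportion of patients that would need an infiltrative technique after a proper rehabilitation protocol". The Aims list in the Methods puts the efficacy of rehabilitation third.
- **Endpoint.** Outcome measurements and assessments lists first among the secondary endpoints: "Proportion of patients for which the tendon needling is not necessary after rehabilitation protocol". The Abstract also counts the rehabilitation success rate among the main secondary endpoints.
- **Missing data.** Statistical analysis states: "Patients with missing data for any of the secondary outcomes will be kept on the study, but excluded from the corresponding analysis". The same section states: "All analyses will be performed with an intention-to-treat analysis".
- **Patients not needled.** Study treatments and interventions first covers success: "If the rehabilitation protocol enables symptom disappearance (i.e., the rehabilitation was successful), the intervention will not be performed". It then adds: "If, for any other reason, the intervention cannot be performed, the patient will be dropped out of the study".
- **Assessment times.** Table 1 places the rehabilitation efficacy assessment only at the last rehabilitation visit and at the extra visit for those whose programme is lengthened.
- **Size.** Study design states: "This study will include 232 patients and will be conducted in two steps". The Sample size section assumes 75% rehabilitation success and 10% dropout.

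No section names the denominator of the rehabilitation proportion or says how a patient lost during rehabilitation is counted.

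**The concern.** A patient who stops attending before the end-of-rehabilitation assessment has no value for this endpoint. Under the missing-data rule as worded, that patient leaves the analysis. The proportion then describes patients who were assessed, whereas the aim concerns all patients given the programme.

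The estimate has no comparison arm in which such a loss could cancel, so any link between leaving and outcome passes directly into the reported rate. The Discussion intends to publish the case series together with the randomised trial as a basis for clinical recommendations. An error here would misstate how many patients go on to need an infiltrative technique.

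The rule that drops patients who cannot be needled raises a second, separate question. Some of these patients will have a known rehabilitation outcome, namely failure. Their data are not missing, so the missing-data rule does not touch them. The plan does not say whether being dropped from the study also removes them from this denominator.

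**Working it through.** **The plan's own figure.** With a difference of 10 points, an SD of 10 points, two-sided alpha 5% and power 95%, n per arm = 2 × (1.960 + 1.645)² × (10/10)² = 25.99, so 26 per arm and 52 in total. Then 52 / 0.90 = 57.8, so 58 randomised, and 58 / (1 − 0.75) = 232. The stated 232 is reproduced and does not depend on the missing-data rule.

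**Inputs.** N = 232 and 75% success, hence 174 successes and 58 failures (Sample size). The share lost during rehabilitation is not given. I assume 10%, the plan's only dropout figure, and also show 5% and 20%. At 10%, 23 are lost and 209 are assessed.

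**Complete-case rate.** Let f be the share of failures among the 23 lost. The observed rate is (174 − 23(1 − f)) / 209.

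| f | Observed rate | Bias (points) |
|---|---|---|
| 0 | 151/209 = 72.2% | −2.8 |
| 0.25 | 156.75/209 = 75.0% | 0 |
| 0.50 | 162.5/209 = 77.8% | +2.8 |
| 0.75 | 168.25/209 = 80.5% | +5.5 |
| 1 | 174/209 = 83.3% | +8.3 |

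At a true 75%, the room for upward bias is three times the room for downward bias. The apparent need for infiltration, truly 25%, would be reported as anything from 27.8% to 16.7%.

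**Other loss rates.** At 5% (12 lost, 220 assessed) the range is 162/220 = 73.6% to 174/220 = 79.1%. At 20% (46 lost, 186 assessed) it is 128/186 = 68.8% to 174/186 = 93.5%. The last figure needs every lost patient to be a failure and is an extreme bound.

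**Against sampling error.** The 95% CI half-width at 75% and n = 232 is 1.96 × √(0.75 × 0.25 / 232) = 5.6 points. At 10% loss the bias reaches this size when 151 + 23f = 209 × 0.8057 = 168.4, so f = 17.4/23 = 0.76. About three quarters of the lost must be failures, against 25% of all patients.

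**Known failures dropped.** If k patients with known failure leave the denominator and nobody else is lost, the rate is 174/(232 − k). One such patient gives 174/231 = 75.3%, and every further one raises it. This effect has only one direction.

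**Counting every lost patient as a failure.** The estimate is (174 − 23(1 − f)) / 232: 65.1% at f = 0, 67.6% at f = 0.25, 70.0% at f = 0.50 and 75.0% at f = 1. Writing x = 151 + 23f, its absolute bias equals that of the complete-case rate when x(1/209 + 1/232) = 1.5, so x = 164.9 and f = 13.9/23, about 0.6. Below that share the complete-case rate is closer to the truth, and above it the worst-case count is closer.

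**What the reader of the results could recover.** If 157 of 209 assessed patients (75.1%) are successes, the rate over all 232 lies between 157/232 = 67.7% and 180/232 = 77.6%.

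**The case against.** **The rule may not have been meant for this endpoint.** The missing-data paragraph follows text on between-group tests, where secondary outcomes are described as changes from baseline, and that baseline is month 0. The rehabilitation proportion is neither a change from month 0 nor a comparison of groups. This stands as a possible reading. The sentence is nevertheless unrestricted, the endpoint is on the secondary list, and the narrower reading leaves the endpoint with no stated denominator. A condensed article may leave that detail to the full protocol, so the point rests on what the printed rule literally does.

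**Loss may be small.** Data collection and management provides for rebooking missed appointments and for continued data collection after protocol deviations. Leaving the exercise programme is therefore not the same as a missing outcome. This limits the size of the problem but does not settle how remaining losses are counted.

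**A reader might infer that the success rate is likely overstated.** The documents do not support that. They give no loss rate for rehabilitation and no reasons for leaving, and patients who recover may also stop coming, which lowers the rate.

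**A reader might infer a clear conflict with intention-to-treat.** The section does apply the term to all analyses. It naturally refers to randomised groups, however, and an unrandomised proportion has no allocation to preserve, so I do not rely on it.

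**Failure imputation can be worse than the rule.** This is correct, as the working shows, and it is why bounds are preferable to a single imputed headline.

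**Conclusion.** The point holds as a defect of the printed rule. As worded, it turns the estimate for the first aim into one restricted to patients with known status, and the separate drop-out rule may also remove known failures. The first effect can go either way, with more room upward. The second can only raise the rate.

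At a true 75% and 10% loss, the complete-case rate lies between 72.2% and 83.3%. The bias exceeds the 5.6-point half-width only if about 76% or more of the lost are failures. Smaller biases would still shift the estimate without showing in its confidence interval.

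These sizes rest on the plan's 75% and on a loss rate that is my assumption. The Abstract's target of 58 randomised is exactly 25% of 232, which suggests that the 10% was meant for the period after allocation. The randomised month-3 comparison and the figure of 232 are not affected.

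**What to change.** In Statistical analysis, exempt the rehabilitation success proportion from the exclusion rule and define its denominator as all patients who start rehabilitation.

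- Patients with known unsuccessful rehabilitation who are not needled stay in the denominator and count as not successful. Reconcile the drop-out sentence in Study treatments and interventions with this.
- For patients with unknown status, report the proportion over all starters with both bounds (all lost = failure, all lost = success), alongside the complete-case figure and the number lost.
- Before computing the proportion, reconcile the two descriptions of the outcome. Success is tied to symptoms in "If the rehabilitation protocol enables symptom disappearance (i.e., the rehabilitation was successful), the intervention will not be performed", while allocation is tied to satisfaction in "if patients are not satisfied, they will be allocated to the PRP or saline group". A patient who is satisfied but not free of symptoms is placed by neither.

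This costs a few sentences and needs no extra patients or visits. The downside is that the worst-case bound understates success if many of those lost had recovered: 151/232 = 65.1% against a true 75% if all 23 had. It should therefore be read together with the best-case bound.
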